# Acute neurological care in north-east Germany with telemedicine support (ANNOTeM): protocol of a multi-center, controlled, open-label, two-arm intervention study

**DOI:** 10.1186/s12913-020-05576-w

**Published:** 2020-08-17

**Keywords:** ANNOTeM, Emergency medicine, Health care research, Neuro acute units, Quality management, Stroke / Neurological disease, Telemedicine

## Abstract

**Background:**

Both diagnosis and treatment of neurological emergencies require neurological expertise and are time-sensitive. The lack of fast neurological expertise in regions with underserved infrastructure poses a major barrier for state-of-the-art care of patients with acute neurological diseases and leads to disparity in provision of health care. The main purpose of ANNOTeM (acute neurological care in North East Germany with telemedicine support) is to establish effective and sustainable support structures for evidence based treatments for stroke and other neurological emergencies and to improve outcome for acute neurological diseases in these rural regions.

**Methods:**

A “hub-and-spoke” network structure was implemented connecting three academic neurological centres (“hubs”) and rural hospitals (“spokes”) caring for neurological emergencies. The network structure includes (1) the establishment of a 24/7 telemedicine consultation service, (2) the implementation of standardized operating procedures (SOPs) in the network hospitals, (3) a multiprofessional training scheme, and (4) a quality management program. Data from three major health insurance companies as well as data from the quality management program are being collected and evaluated. Primary outcome is the composite of first time of receiving paid outpatient nursing care, first time of receiving care in a nursing home, or death within 90 days after hospital admission.

**Discussion:**

Beyond stroke only few studies have assessed the effects of telemedically supported networks on diagnosis and outcome of neurological emergencies. ANNOTeM will provide information whether this approach leads to improved outcome. In addition, a health economic analysis will be performed.

**Study registration:**

German Clinical Trials Register DRKS00013067, date of registration: November 16 th, 2017, URL: http://www.drks.de/DRKS00013068

## Background

The implementation of stroke units [1] along with the advent of intravenous thrombolysis [1] as well as thrombectomy of large vessel occlusion [2] has led to a huge leap in evidence-based acute stroke therapy. However, treatment effects are time-sensitive and depend on swift application of specific therapies. This is not only true for stroke but also for other neurological emergencies like seizures, meningoencephalitis, and spinal cord injury, where fast and effective diagnostication and treatment have been shown to improve outcome [3–5]. Neurological emergencies are a major cause of functional dependence [6]. Hospitals with emergency departments but without a neurology sercive may struggle to provide up-to-date care for patients with neurological emergencies. This applies particularly to rural and other regions with underserved infrastructure. Unfortunately, most neurological diseases peak at higher age, which means that rural areas with typically elderly populations face a particular challenge in providing appropriate care.

Telemedicine networks offer the potential for providing neurological expertise for emergency departments without expert neurologists [7]. In fact, neurological diseases can be adequately assessed via audiovisual examination because typical neurological deficits like palsies, disturbances of speech or consciousness can be reliably captured via video stream [8, 9] and brain imaging is easily transferable digitally.

Telestroke networks have been developed as a blueprint for teleneurological treatment during recent years. Treatment of acute stroke using telemedicine resulted in more frequent and appropriate application of intravenous thrombolysis [10, 11] and was associated with improved outcome [12]. What is more, “telestroke” proved to be cost-effective [13] making stroke one of the most frequent indications for telemedicine in several countries (Refs als from US, Germany etc).

### Aims

ANNOTeM (acute neurological care in North-East Germany with telemedicine support) aims to improve health care by use of telemedicine for acute time-dependent neurological diseases beyond stroke, in particular coma/status epilepticus, meningoencephalitis, and spinal cord injury, and therefore establish sustainable structures for implementation of evidence based treatments in underserved areas in North-East Germany.

## Methods/design

### Hypothesis

A multi-component intervention with telemedicine support for neurological emergency care extends time to death or first time of receiving paid outpatient nursing care or first time of receiving care in a nursing home within 90 days after hospital admission.

### Study design and setting

ANNOTeM is a multi-center, controlled, open-label, two-arm intervention study. Primary and secondary outcomes will be evaluated for pre- and post-implemention of the network. The ANNOTEM intervention started in November 2017 and is expected to run until the end of July 2020.

### Conventional care

Community hospitals, except one without a neurology department, were included in the teleneurological network if they had treated a significant number of at least 50 patients per year with main discharge diagnosis of an acute neurological disease. During the control period, patients had usually been admitted to the internal medicine department and had been seen by a neurologist the following day at the earliest. Typically, management of acute neurological diseases had not been based on standardized operating procedures (SOP) in these hospitals prior to the project.

### Intervention

#### Structure of the network

The teleneurological network ANNOTeM consists of a consortium of four neurocenters (Charité -Universitätsmedizin Berlin, Universitätsmedizin Greifswald, Unfallkrankenhaus Berlin, Epilepsieklinik Tabor) with neurological and epileptological expertise, three health insurance companies (Allgemeine Ortskrankenkasse Nordost, Potsdam (AOK Nordost), Barmer Ersatzkasse, Wuppertal (BARMER), Techniker Krankenkasse, Hamburg (TK)), one technology partner specialized on telemedicine communication products (MEYTEC, Werneuchen, Germany) and the Institute of Public Health, Charité -Universitätsmedizin Berlin,as evaluating institute. The consortium is led by the Charité - Universitätsmedizin Berlin. The clinical centers provide teleneurological care to 11 regional hospitals in the northeastern federal states of Germany (2 in Mecklenburg-Western Pomerania, 8 in Brandenburg and one in Saxony-Anhalt). One regional hospital runs its own neurological department with a certified regional Stroke Unit. In the ten hospitals, the “Neuro Acute Units” were set up as part of the intervention and managed by the respective departments of internal medicine in nine hospitals, whereas in the remaining hospital the “Neuro Acute Unit” is managed as part of an interdisciplinary intensive care unit. In addition, the network cooperates with other neurological, neuroradiological and neurosurgical facilities in the region.

#### Neuro-acute-units

The structure of the “Neuro-Acute-Units” is based on the concept of the German Tele-Stroke-Units [14] and aims at specialized treatment for a broader spectrum of acute neurological diseases. In addition to the standards already defined for Tele-Stroke Units, quality management, training, courses, and bed-side visits will be extended to the management other acute neurological diseases considered as part of the intervention for physicians, nurses and therapists.

#### Implementation of standardized operating procedures

Standardized operating procedures (SOP) for management of acute stroke, epileptic seizures/epilepsy, meningitis/encephalitis, and acute spinal cord injury were developed by consensus of the four neurocenters [15, 16]. These SOPs are generally based on the guidelines of the German Neurological Society (Deutsche Gesellschaft für Neurologie, DGN) und Joint Workgroup of German Medical Societies (Arbeitsgemeinschaft der Wissenschaftlichen Medizinischen Fachgesellschaften, AWMF), but had to be adapted in some aspects with regard to the telemedicine setting. Furthermore, they undergo regular updates according to the evolving scientific evidence. Before initiating teleconsultations, each SOP was presented to each team of the network hospitals followed by a discussion of their implementation in clinical routine.

#### Quality management

With start of the network, each cooperating community hospital started documentation of quality indicators within the quality assessment for stroke in Northwest Germany (*Qualitätssicherung Schlaganfall Nordwestdeutschland*, based on the *Arbeitsgemeinschaft Deutschsprachiger Schlaganfall Register* (ADSR)). The ANNOTeM network developed additional quality assessment instruments for other acute neurological diseases (epilepsy, meningitis/encephalitis, and spinal cord injury) for their use in the regional hospitals.

In addition to quality assessment, regular meetings on treatment quality are held in the cooperating regional hospitals with mutual discussion of the proportions of patients presented via telemedicine, documentation rates as well as the SOP-adherence and interhospital transfers of patients.

#### Teleneurological consultations

Teleneurological consultations are provided by physicians who are experienced in stroke treatment and meet the standard of board certified neurologists for diagnosis and treatment of neurological emergencies. The consultation service is staffed 24/7 by a full-time physician. All physicians working in the telemedicine service receive a practice training for the technical system as well as for the procedures of teleneurological examination and treatment of patients. The cooperating regional hospitals can present all patients with acute neurological symptoms in teleconsultation. For this purpose, a hotline is used to contact the telemedicine centers. The patient is examined via video conference with remote-controlled camera together with the onsite physician. In addition, there is a connection to the imaging data systems of the cooperating regional hospitals. This can be used to forward any computer tomography (CT) or magnetic resonance imaging (MRI) images to a central Picture Archiving and Communication System (PACS), accessible from the teleneurology hubs. The data transfer in ANNOTeM is realized as a point-to-point connection between the respective active neurocentres and the regional cooperation hospitals (see Fig. 1). All connections are encrypted according to state-of-the-art data protection requirements (GDPR, General Data Protection Rules). Data are stored on secured servers with access restricten to staff of the medical project management. Video streams are not stored. After each consultation, a written statement with recommendations for acute treatment and further diagnostic procedures is sent electronically (PDF) to the regional hospital and printed automatically. During the monitoring on the neuro-acute unit, a board certified neurologist sees the patient during ward rounds on a daily basis.

**Fig. 1 Fig1:**
[figure not shown]
Representation of data flows in the telemedical network ANNOTeM. The video data is transmitted as a stream using a point-to-point connection, while the documentation and other examination data are stored in a central repository. With permission of MEYTEC GmbH, the telemedical equipment used in ANNOTeM is shown (left: VIMED TELEDOC, right: VIMED DOC)

#### Transfer management

Patients who need specialized treatment beyond the capacities of the implemented “Neuro-Acute-Units” (in particular patients with need for neuroradiological or neurosurgical treatment, not being available in regional network hospitals) are transferred to the nearest suitable hospital. In order to avoid delays in the referral hospital, point-to-point connections have been established between the telemedicine centres and the various referral hospitals, allowing the transmission of imaging data collected in network hospitals. In addition, referral hospitals report data on processes and in-hospital outcomes for the respective patients to the coordinating center.

### Study population

#### Inclusion criteria

To determine the composite primary outcome of time to death or first-time care at home or paid care support for the first time within 90 days after the index event, we will use routine data from three cooperating health insurance companies (AOK Nordost, BARMER, TK). For this purpose, eligible study participants must (1) have continuous health insurance with one of these health insurers during the evaluation period, (2) be admitted during the intervention or control period to one of the cooperating regional hospitals, (3) have a neurological diagnosis (International Classification of Diseases (ICD)-10 main diagnosis) such as stroke (I60–64), status epilepticus or impaired level of consciousness (G41, R40), meningitis /encephalitis (A82.0–2, A85–87, G00–03, G06–09), acute spinal cord injury (S14, S24, S34, G82), (4) and be over 18 years of age of both sexes.

We had originally planned to include patients diagnosed with traumatic brain injury (S06–07) in an earliert version of the study protocoll. However, since patients with traumatic brain injury are only rarely managed by our project partners in the participating regional hospitals they are not included in the primary study population, but rather as a companion study population in a sensitivity analysis.

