#### Comparison with non-participating hospitals

In order to investigate whether differences in outcome in the cooperating hospitals may be caused by temporal trends, the composite primary outcome will also be analysed for the same two periods in patients fulfilling the identical inclusion criteria but being treated in hospitals of the same region that do not participate in the network (non-network community hospitals). The non-network hospitals were matched according to geographical location, size and amount of acute neurological cases per year. Data for this comparison are also provided by the three insurance companies.

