### Statistical analyses

#### Primary analysis

Because health insurance data will be provided anonymously, we cannot determine the effect of telemedicine consultation on an individual patient level. Rather, we will evaluate the effects of the ANNOTeM concept in clusters. The primary outcome will be analysed as the time from the index visit to the occurrence of the compound outcome as described above. Separate Cox models will be fitted for eligible patients insured at the cooperating health insurance companies, admitted and treated in both, the pre-implementation period and the intervention period. Cox models will comprise sex (m/f only), age and co-morbidity (Y/N) as covariates. Hazard rate ratios will be used to compare time-to-compound event between the two periods. All tests will be performed at a significance level of alpha = 0.05, adjusted for two-sided testing and the k = 6 tests of the primary and secondary analysis. All tests will be performed using the statistics package ‘R’ (version 3.6).

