#### Secondary analysis

The secondary analysis compares the survival rates obtained in the primary for the network clinics with the group of non-cooperating hospitals using the log-rank-test for 2 × 2 factorial designs (control vs intervention period and network vs non-network hospitals). A treatment effect will be revealed by a significant interaction in favour of the network clinics during the intervention period.

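### Groups are defined by the admitting hospital, so a change in who arrives once the Neuro Acute Units open may be read as a treatment effect; the same-region comparison does not correct this and can amplify it

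*Protocol article*

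**What the plan says.** Under Inclusion criteria (Protocol article), patients must "be admitted during the intervention or control period to one of the cooperating regional hospitals". The Intervention group and Control group sections repeat this hospital-based definition for the two periods. None of these sections uses residence or catchment.

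Between the periods the hospitals change. Structure of the network says that Neuro Acute Units "were set up as part of the intervention and managed by the respective departments of internal medicine in nine hospitals", with a tenth unit inside an interdisciplinary intensive care unit. Teleneurological consultations describes a service staffed at all hours. Under Conventional care, control-period "patients had usually been admitted to the internal medicine department and had been seen by a neurologist the following day at the earliest".

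The parallel comparison uses patients "treated in hospitals of the same region that do not participate in the network". On the choice of those hospitals: "The non-network hospitals were matched according to geographical location, size and amount of acute neurological cases per year". Secondary analysis, which names a log-rank test for a 2 × 2 design, reads the result this way: "A treatment effect will be revealed by a significant interaction in favour of the network clinics during the intervention period". For adjustment, Primary analysis states: "Cox models will comprise sex (m/f only), age and co-morbidity (Y/N) as covariates". The limitations in the Discussion present the parallel control as a remedy for time trend. The only patient selection discussed there is selection through informed consent.

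**The concern.** Membership of the intervention-period group is decided at arrival, after the new unit could already have influenced arrival. A hospital that gains neurological cover at all hours may receive patients who would previously have gone elsewhere. If they differ in baseline risk from those who came before, the event rate moves without any effect of care. This happens before treatment and is distinct from changes in coding and from transfers after admission.

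A concurrent control removes a trend that is common to both sets of hospitals. It does not remove a shift confined to the network hospitals. If the redirected patients come from the comparators, those hospitals' case mix changes too. At stake is the rule that a significant interaction reveals a treatment effect, because that rule sets no condition on stable patient flow.

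**Working it through.** **Inputs from the article.** Sample size calculation gives 39% in the control period and 32% in the intervention period, so the planned difference is 39 - 32 = 7 points. It also gives at least 1820 patients per group.

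**Assumptions, because the article gives no figures.** There is no true effect, and the risk is 39% in network and comparator hospitals before the intervention unless stated. A share *s* of intervention-period network admissions is redirected, with risk *r*. The number of other admissions is unchanged, and no covariate adjustment is applied. A proportion *c* of the redirected patients comes from comparators whose control-period volume is *S* times the network's.

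**Formulas.**
- Network after the shift: (1 - s) × 39 + s × r
- Redirected patients per original network patient: m = s / (1 - s)
- Share of patients lost by the comparators: L = m × c / S
- Comparators after the shift: (39 - L × r) / (1 - L)
- Controlled contrast: network change minus comparator change

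**Central illustration, s = 10%, r = 29%.**
- Network: 0.9 × 39 + 0.1 × 29 = 38.0, a before-after bias of -1.0 point.
- No redirected patients from comparators (c = 0): comparators stay at 39, so the contrast is -1.0.
- All from equally large comparators (c = 1, S = 1): m = 0.1 / 0.9 = 0.111, and comparators become (39 - 0.111 × 29) / 0.889 = 40.25. The contrast is -1.0 - 1.25 = -2.25 points, and 2.25 / 7 is about one third of the planned difference.

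**Range with c = 1 and S = 1.**

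| s | r | Before-after bias | Controlled contrast |
|---|---|---|---|
| 5% | 34% | -0.25 | -0.53 |
| 10% | 29% | -1.0 | -2.25 |
| 20% | 24% | -3.0 | -8.0 |
| 5% | 49% | +0.5 | +1.06 |
| 10% | 49% | +1.0 | +2.25 |
| 20% | 49% | +2.0 | +5.33 |

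The 20% rows require the comparators to lose 0.20 / 0.80 = 25% of their patients, which is extreme.

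**Dependence on where the patients come from, s = 20%, r = 25%.** The before-after bias is -2.8. The contrast is -7.5 if all come from equally large comparators, -4.1 if the comparators are three times as large, -3.5 if five times as large, and -2.8 if none come from them.

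**A case where the comparison helps.** Take s = 20%, r = 33%, and comparators at 30% before. The network change is 0.8 × 39 + 0.2 × 33 - 39 = -1.2. With L = 0.25 the comparators become (30 - 0.25 × 33) / 0.75 = 29.0, a change of -1.0. The contrast is -0.2.

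**Scale.** With 1820 independent patients per group and an unadjusted two-sided 5% level, a comparison of proportions from 39% has 80% power for about 4.5 points. Redirection alone produces a 4.5-point fall when s = 0.045 / (0.39 - r): 19% for r = 15%, 24% for r = 20%, 32% for r = 25%. These are risk differences; the planned analyses work on hazards and survival curves.

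**The case against.** The strongest reply is that the mechanism is conjecture. The article reports no bypassing, ambulance routing or change in admissions. Conventional care says that the included hospitals already treated at least 50 such patients a year. That stands: redirection is a possibility, and its direction is not known.

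A reader might infer that the same-region comparison necessarily amplifies the bias, or that it is always worse affected than the primary analysis. The article does not support this. The comparators are community hospitals matched on size and case volume as well as location. Patients who bypassed a local hospital for lack of neurology may have gone to larger centres instead. The contrast then equals the before-after bias, and the last example above shows that it can also be smaller.

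A reader might also infer that ten hospitals had no neurological input before the network. The article says only that they had no neurology department and that a neurologist came the next day at the earliest. Its planned subgroup by earlier neurological departments or telemedicine support suggests that some may have had support already, so the change in attractiveness may be modest there.

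Partial safeguards exist. The Cox covariates absorb some of any shift, the subgroups (earlier neurological support, stroke against other diagnoses, prior care) are indirect checks, and the insurer data already contain admission counts. None of these is directed at patient flow, and none qualifies the rule for reading the interaction.

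**Conclusion.** The point holds in conditional form. Groups are defined by a hospital of arrival that the intervention may influence. The named covariates include no severity measure, and the non-network comparison addresses time trend, not redirection. A differential change in who is admitted could therefore be read as an effect or hide one.

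Under the central assumptions the bias is -1.0 point before-after. In the controlled contrast it lies between -1.0 and -2.25 points, depending on whether none or all of the redirected patients come from equally large comparators. With redirected patients at 49% risk the sign reverses. The shares and risks are assumed, and covariate adjustment would reduce the figures. They show what the design would leave undetected; they do not estimate what happened. A reader might conclude that redirection took place or that it favours the network. The article supports neither. The weakness warrants a change to the interpretation rule and a check, but does not invalidate the primary analysis.

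**What to change.** Keep the hospital-based primary analysis and make two additions.

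(a) Compare qualifying admissions, diagnosis mix, age, sex, co-morbidity and prior-care status by hospital and period, in network and comparator hospitals. Amend Secondary analysis so that a significant interaction is read as a treatment effect only together with this comparison, and as possibly due to changed patient flow if volumes or case mix shift differently in the two sets of hospitals. This should need little beyond the data the insurers already supply.

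(b) Add one supportive sensitivity analysis by place of residence. Catchments of network and comparator hospitals are fixed from control-period admissions. The insurers derive a catchment flag before anonymisation, assuming they hold postcodes, and pass on no postcode. The population is all insured residents of those catchments with a qualifying diagnosis, whichever hospital first admitted them. The model is a Cox regression with a period-by-network-catchment interaction. It must be specified as a new model, because the current secondary analysis is a log-rank test.

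Attribution should not depend on the sign of the residence-based estimate. Residents treated elsewhere dilute it and make it less precise, so it serves only as a check. The main cost is a wider extract covering other admitting hospitals, for which the existing approval of the data transfer may have to be extended.

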#### Intervention group (post-implementation)

The intervention group consists of patients treated in one of the eleven cooperating regional hospitals diagnosed with any of the acute neurological diseases (stroke, seizures/status epilepticus, meningoencephalitis, and spinal cord injury) defined in inclusion criteria between November 2017 and July 2020.

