#### Control group (pre-implementation)

Patients included in the control group were admitted and treated with one of the above mentioned acute neurological diseases in the same cooperating regional hospitals between November 2014 and May 2017, i.e. before start of the ANNOTeM implementation.

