#### Sensitivity analysis

In a sensitivity analysis, we extend the follow-up of the composite primary outcome to 120 days after the index event. Secondly, we perform separate analyses for the outcomes death, first-time nursing home care and paid nursing care for the first time, which together make up the composite endpoint in the primary analysis. Thirdly, we perform a subgroup analysis of the composite primary outcome for following groups: patients with stroke vs other defined acute neurological diseases; patients with vs without nursing care before the index event; patients in cooperating hospitals with vs without neurological departments or telemedicine support before the start of the ANNOTeM intervention. Finally, we investigate patients in the cooperating hospitals with traumatic brain injuries who cannot be included in the main intervention group as a companion study population.

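### The ICD-10 eligibility list does not match its own labels for meningitis/encephalitis and acute spinal cord injury; the effect is dilution and mislabelling, mainly of the non-stroke group

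*Protocol article*

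**What the plan says.** Under Inclusion criteria, the protocol article requires that patients "have a neurological diagnosis (International Classification of Diseases (ICD)-10 main diagnosis) such as stroke (I60–64" and so on through the other groups. The two groups at issue are coded as "meningitis /encephalitis (A82.0–2, A85–87, G00–03, G06–09), acute spinal cord injury (S14, S24, S34, G82".

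Other sections lean on this list:

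- **Intervention group** refers back to it: "stroke, seizures/status epilepticus, meningoencephalitis, and spinal cord injury) defined in inclusion criteria".
- **Control group** does the same for the earlier period: "treated with one of the above mentioned acute neurological diseases in the same cooperating regional hospitals".
- **Comparison with non-participating hospitals** applies the same criteria there.
- **Data collection methods** has the insurers supply data according to these criteria.

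The Aims describe the target as "acute time-dependent neurological diseases beyond stroke", "in particular coma/status epilepticus, meningoencephalitis, and spinal cord injury". The section on standardized operating procedures states that procedures for "epileptic seizures/epilepsy, meningitis/encephalitis, and acute spinal cord injury were developed by consensus". The Sensitivity analysis section plans a subgroup comparison of "patients with stroke vs other defined acute neurological diseases".

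**The concern.** Insurance records are the only route into the study, and they are searched by main-diagnosis code. Whatever the labels say, the codes decide who is analysed. If codes and labels differ, the analysed population is not the one that the aims and the operating procedures describe.

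Extending the telestroke model to other emergencies is the stated novelty of the project. Meningoencephalitis and spinal cord injury are two of the three conditions beyond stroke that the Aims name. In the planned analyses, the stroke-versus-other subgroup is the one that isolates the non-stroke patients. Losing some encephalitis patients, and adding patients with old paralysis or a peripheral nerve injury, changes whom that result describes and would tend to pull an effect in that group towards the null.

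**Working it through.** **Step 1. What the document shows without any outside source.** In the list labelled meningitis/encephalitis, the G codes run 00–03 and then 06–09, so 04 and 05 are missing. The A codes run from 82 to 85, so 83 and 84 are missing. No reason is given for either gap. Under acute spinal cord injury, S14, S24, S34 and G82 are entered as whole three-character categories, with no limit by subcode or acuity. Subcodes were available to the authors, since A82 is given at that level.

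**Step 2. What the codes cover.** The document prints no code titles. The readings below are the usual ones in the classification that the criterion invokes. They are an assumption until checked against the catalogue version in use.

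| Label in the plan | Code | Status | Usual reading |
|---|---|---|---|
| Meningitis/encephalitis | G04 | omitted | encephalitis, myelitis, encephalomyelitis |
| | G05 | omitted | companion category to G04, rarely a main diagnosis |
| | A83–84 | omitted | mosquito- and tick-borne viral encephalitis |
| | A85–86 | included | other and unspecified viral encephalitis |
| | A82.0–2 | included | rabies; the .2 subcode does not appear to exist |
| | G09 | included | sequelae of inflammatory CNS disease |
| Acute spinal cord injury | S14, S24, S34 | included whole | cord injury, and also nerve-root, plexus and peripheral nerve injury |
| | G82 | included whole | para- and tetraplegia of any duration |

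**Step 3. Patients lost.** The document expects at least 1820 patients per group and gives no split by diagnosis. Every share below is an assumption.

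- Non-stroke share 10% to 25%: 1820 × 0.10 = 182; 1820 × 0.25 = 455.
- CNS infection 10% to 25% of these: 182 × 0.10 = 18; 455 × 0.25 = 114.
- Omitted codes 20% to 50% of CNS infection: 18.2 × 0.20 = 3.6; 113.75 × 0.50 = 56.9.

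That is about 4 to 57 patients per group. Of the whole group it is 3.6/1820 = 0.2% to 56.9/1820 = 3.1%. Of the non-stroke patients it is 0.10 × 0.20 = 2% to 0.25 × 0.50 = 12.5%.

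**Step 4. Patients added.** No count can be derived. To show how the effect scales, let a share f of those analysed be outside the target condition, with the control risk of 39% and no benefit. The planned fall from 39% to 32% (7 points) then becomes 7 × (1 − f) points.

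| f, share of the whole sample | Intervention risk | Power at 1820 per group, two-sided 0.05 | Power at 0.05/6 |
|---|---|---|---|
| 0% | 32.0% | 99.3% | 96.2% |
| 5% | 32.35% | 98.7% | 94.0% |
| 10% | 32.7% | 97.8% | 90.8% |
| 20% | 33.4% | 94.0% | 81.0% |

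The 0.05/6 column reads the plan's adjustment for six tests as a Bonferroni division. The power at f = 0 is well above the stated 80% because 39% versus 32% needs only 733 per group for 80% power at two-sided 5%. The 1820 is therefore used here as the expected caseload. That discrepancy is a separate matter and does not bear on the codes.

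A misfit confined to two small non-stroke groups gives a small f for the whole sample. Within the non-stroke patients, the same number of misfits is a share 4 to 10 times as large (1/0.25 to 1/0.10), so the attenuation falls there.

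**Step 5. Direction.** One list governs both periods and both sets of hospitals. The mismatch is therefore non-differential: it alters who is studied, not how the periods are compared.

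**The case against.** The strongest objection is that the document prints no code titles, so the substantive steps rest on the classification and not on the plan. This stands in part. The gaps and the unrestricted categories are visible in the text, but their meaning must be confirmed by lookup. The criterion names ICD-10 as its own definition, however, so a lookup settles the matter.

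A second objection is that the codes are introduced only as examples and that a condensed article may abbreviate a longer list. This carries less weight. Later sections refer to the diseases as defined by these criteria and apply the same criteria to other hospitals and to the data request. The point is that a specific list is printed and does not fit its labels, not that detail is absent.

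A third objection is that the effect is small and non-differential, and that the non-stroke subgroup also contains status epilepticus and impaired consciousness (G41, R40). This stands and limits the finding.

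A reader might also infer more than the documents support:

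- **That encephalitis is left out altogether.** It is not: on the same reading, A85–86 are viral encephalitis and are listed.
- **That the two groups consist largely of the wrong patients.** There are no counts by code, and the listed categories also hold meningitis and true cord injury.
- **That the period comparison is biased.** The same list applies on all sides.
- **That patients already in care cannot reach the endpoint.** They can die, and those cared for at home can first enter a nursing home. Care status at the start is recorded, and a subgroup by prior care is planned.

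**Conclusion.** The concern holds in a limited form. The printed list is a stated eligibility rule that does not match its labels. It leaves out some encephalitis categories and lets in sequelae, non-acute paralysis and nerve injuries outside the cord. The consequence is dilution and mislabelling, mainly on the non-stroke side of the subgroup analysis; the overall hazard ratio should move little. The loss of 4 to 57 patients per group depends entirely on the three assumed shares, and the number wrongly included is unknown. The conclusion also assumes the usual ICD-10 readings. It is worth correcting because the change is cheap and decides whom the beyond-stroke result describes.

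**What to change.** Before the final extraction, check the Inclusion criteria list against the ICD-10 version that the insurers use, then:

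- add G04 (with G05 for completeness) and A83–84, or state why they are left out;
- drop G09;
- correct the A82 subcode range. A faulty subcode is no reason to delete the category;
- restrict S14, S24 and S34 to their cord-injury subcodes, and G82 to acute subcodes where the catalogue distinguishes them. Otherwise relabel the group so that its name fits its contents;
- apply the one revised list to both periods and to network and non-network hospitals.

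The cost is a revised data request to three insurers, a re-run extraction and a short change to the protocol text. No further patients or follow-up are needed. The article puts the last follow-up at the end of October 2020 and the final analysis in January 2021, so the change belongs before that extraction. It should be justified from the catalogue alone and not from outcome data.
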